### **Research Structure:**

In this single-arm pilot program, we will enroll 100 AA male participants from the annual AAMWI walk/health fair who have poor or average cardiovascular health ( $< 4$  LS7 metrics in the ideal range) with the goal of accomplishing aims exhibited in Figure 2. Our intervention involves two components: a community health worker (CHW) and peer team. Each participant will be assigned to a CHW and grouped into a team of 10 participants based on participant proximity to a central meeting location (total 10 teams). The CHW will assist in activating individual participants to engage in primary care, social support services, and enrollment in ResearchMatch. Within the teams, health coaches will assist the study team in implementing the community-based lifestyle intervention spanning LS7 principles and ResearchMatch, as shown in Figure 2 below.

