### Instructors:

Each team will also be assigned four health coaches, two medical students, one undergraduate student and one nursing student, all of whom are identified from a database of volunteers from the OSU chapters of the Student National Medical Association (SNMA), Minority Association of Pre-Medical Students (MAPS) and Nursing Students Promoting Initiatives Reinforcing Equity (NSPIRE). Medical students will lead the student volunteer teams given their OSU College of Medicine training in health coaching. All instructors will have basic competency of curriculum and protocol.

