### Intervention:

The intervention is a 24-week community-based lifestyle intervention to improve cardiovascular health among AA males involving two components: a CHW and peer team. Each participant will be assigned to a CHW and grouped into a team of 10 participants based on participant proximity to a central meeting location (i.e. Columbus Recreation and Parks centers and YMCAs). Each team's four health coaches will deliver content and coaching around the lifestyle intervention described below. The intervention will be applied evenly to all participants. Health coaches will implement the curriculum [Table 1] utilizing resources from the partnering organizations. Health coaches will meet with participant teams weekly for 75 minutes. Key health coach activities include delivering education, establishing and monitoring progress in achieving individual and team-based SMART (specific, measurable, achievable, relevant, and time-bound) wellness goals.

| Weeks | Session topics                                                                                                                                                                                                                                                                                                                                                                                                                                                                                                                                                                                                                                                                                                       | Partners                   | Study Measurements                                                                       |

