#### **Primary outcome: Feasibility and Acceptability**

Descriptive statistics will be used to summarize quantitative data, including subject recruitment rate, retention rate, the degree of intervention adherence, and the average rating of the satisfaction of the intervention, including the content, length, and dose of the intervention. We will conduct content analyses on qualitative data obtained from verbatim transcripts of sessions and open-ended items of the battery. We will independently explore the data for patterns and significant statements that address intervention acceptability in NVivo 12 software. The research team will discuss, compare, and reduce codes iteratively until inter-coder agreement is met ( $\kappa > 80\%$ ). Finally, we will use matrices to compare qualitative and quantitative acceptability data from the questionnaires. A mixed methods approach will lead to better understanding of how the intervention is perceived, along with which/how strategies affect outcomes in patient engagement and health-related outcomes. We expect that intervention is feasible, and AA men will perceive it as acceptable; however, findings may indicate further need to adapt the intervention (e.g., length of intervention).

Secondary outcomes: 1) prevalence of participants with a primary care provider, change in social and patient activation needs; 2) Changes in cardiovascular health as per American Heart Association LS7 Metrics including blood pressure, cholesterol, glucose, smoking, body mass index, physical activity and dietary intake; and 3) prevalence of participants participating in OSU ResearchMatch. For each outcome, we will use mixed-effects linear modeling for repeated measures to (a) test the fixed effect of time, intervention group, and their interaction; (b) derive within-group and between-group contrast estimates on the change from baseline at each follow-up. Within-subject random effects will be included in the model to adjust for within-subject clustering from longitudinal follow-up. We will also adjust for potential confounders by including them as fixed-effects covariates in the model.

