## **Research Protocol:**

### **Creating Healthier Communities – AAMWI & OSU**

All statistical analyses will be performed using either SAS 9.4 or the most current version (SAS Institute, Inc., Cary, NC) or Stata 15 or the most current version (Stata Corporation, College Station, TX). Descriptive statistics (mean, median, standard deviation, proportions, etc.) of each of the collected variables will be estimated overall.

Sample Size and Power Analysis: This is a pilot study so sample size and power calculations were not performed. We will use data from this pilot study to solidify protocol parameters and estimate the degree of attrition that is considered in sample size and power calculation for a full-scale randomized controlled trial.

Missing Data: We expect missing data, for the post-intervention measures, where we expect a 10% attrition rate. We will carefully examine the pattern of the missing data and impute missing data via multiple imputation methods if missing completely at random (MCAR) mechanism is present. The mixed effects modeling approach described earlier allows for data missing at random (MAR). If the pattern of missing data indicates the potential missing not at random (MNAR), pattern-mixture modeling will be used. The robustness of findings under MCAR, MAR, and MNAR mechanisms will be evaluated.

Heterogeneity of Treatment Effect (HTE): To determine if there is HTE, we will extend our analysis models to include statistical interactions between participant factors and treatment and perform Wald tests of the interaction effect. Potential interaction factors include age, income, education level, neighborhood SES, and food insecurity. These analyses will be considered exploratory and thus no additional adjustment of p-values will be undertaken.

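### The secondary-outcome model adjusts only for repeated measures within a man, although the intervention is delivered in ten peer teams; if changes correlate within teams, its standard errors are too small

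*Protocol*

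**What the plan says.** **Design.** Under Research Structure, "we will enroll 100 AA male participants from the annual AAMWI walk/health fair". Each man is "grouped into a team of 10 participants based on participant proximity to a central meeting location" (Intervention), and Research Structure gives the count as ten teams. Under Instructors, "Each team will also be assigned four health coaches". Under Intervention, "Health coaches will meet with participant teams weekly for 75 minutes", and the coaches' tasks include "establishing and monitoring progress in achieving individual and team-based SMART" goals. Each man is also assigned to a community health worker.

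**Analysis.** The secondary-outcomes paragraph of Analysis and Internal Validity specifies a linear mixed model with fixed effects for time, group and their interaction, plus unnamed confounders as fixed covariates. On correlation it says: "Within-subject random effects will be included in the model to adjust for within-subject clustering from longitudinal follow-up". The target is the change from baseline at each follow-up. The paragraph on heterogeneity of treatment effect adds Wald tests of interaction with age, income, education, neighborhood SES and food insecurity. These are labelled exploratory and are not adjusted for multiplicity.

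**Use of the pilot.** Under Sample Size and Power Analysis, "We will use data from this pilot study to solidify protocol parameters" and to estimate attrition for a full-scale randomized trial. No team ICC is mentioned.

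**The concern.** The peer team is one of the two components of the intervention. Men in a team share a neighbourhood, a meeting site, four coaches, session attendance and some goals. These can move a team's blood pressure, weight or activity changes together, and peer support is partly intended to do that. A model whose only random effects are within-subject treats the men's changes as mutually independent.

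If they are not independent, intervals for the mean change are too narrow and p-values too small. The heterogeneity tests are exposed to the extent that the interacting factor itself clusters by team. Because teams are formed by proximity, neighborhood SES probably varies largely between teams, and there the effective information is closer to ten units than to a hundred.

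**Working it through.** **Inputs from the Protocol:** 100 men in 10 teams of m = 10 (10 × 10 = 100, consistent); 10% expected attrition, so about 90 completers, or m = 9 per team. The Protocol states no SD, alpha, power or ICC, so it has no figure of its own to reproduce.

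**Assumptions:** ICC of the change score from 0 to 0.10; two-sided 5% level; equal team sizes.

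**What matters for a change.** A stable difference in level between teams cancels in a within-person change. Only team-level variation in the change itself inflates its standard error. The relevant quantity is therefore the ICC of change, not the ICC of the baseline value.

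**Formulas**
- Design effect: DE = 1 + (m − 1) × ICC
- True SE ÷ unadjusted SE = √DE
- Effective n = n ÷ DE
- Actual error of a nominal 5% test = 2 × [1 − Φ(1.96 ÷ √DE)]

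Example (m = 10, ICC 0.05): DE = 1 + 9 × 0.05 = 1.45; √1.45 = 1.204; 100 ÷ 1.45 = 69; 1.96 ÷ 1.204 = 1.628, giving an error of 0.104.

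| ICC of change | DE (m = 10) | SE ratio | Effective n | Actual error | Actual error (m = 9) |
|---|---|---|---|---|---|
| 0 | 1.00 | 1.00 | 100 | 0.050 | 0.050 |
| 0.01 | 1.09 | 1.04 | 92 | 0.061 | 0.059 |
| 0.02 | 1.18 | 1.09 | 85 | 0.071 | 0.069 |
| 0.05 | 1.45 | 1.20 | 69 | 0.104 | 0.098 |
| 0.10 | 1.90 | 1.38 | 53 | 0.155 | 0.144 |

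Simulating one-sample t-tests on the change score (40,000 trials per setting) agrees. With ten teams of ten the error was 6.0%, 10.1% and 15.6% at ICC 0.01, 0.05 and 0.10. With ten teams of nine it was 5.8%, 9.6% and 14.4%. A t-test on the ten team means (9 df) stayed between 4.8% and 5.1%.

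**Price of the correction.** The 97.5% t quantile is 2.262 on 9 df and 1.984 on 99 df, a ratio of 1.140. Relative to the unadjusted interval, the team-level interval is therefore:
- at ICC 0: 1.140 × 1.000 = 1.14, about 14% wider;
- at ICC 0.05: 1.140 × 1.204 = 1.37, about 37% wider.

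**Does the correction survive a zero variance estimate?** With ten teams of ten, the estimated between-team variance is zero or negative in about 47% of simulated trials at ICC 0.01, 25% at 0.05 and 11% at 0.10. If the analysis then reverts to the unadjusted SE and 99 df, and otherwise uses the team-level SE with 9 df, the overall error is 3.7%, 4.4% and 4.9%. It stays below 5% because reversion happens only when the team-level SE is the smaller of the two.

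**Precision of the ICC.** At a true ICC of 0.05 with ten teams of nine, 95% of simulated estimates lie between about −0.07 and 0.21.

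**The case against.** **The consequence is not certain.** A reader might infer that the standard errors are definitely too small for every 12- and 24-week change. The documents do not support that. They give no ICC, the range above is assumed, and at ICC 0.01 the error is only about 6%. This stands: the omission is certain, its effect is conditional.

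**The reach is limited.** Feasibility and acceptability are summarised descriptively and by content analysis, so the primary objective is untouched. The Protocol sets no alpha and no efficacy success rule; the 5% level is imported here to express size. This also stands.

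**The pilot could still supply an ICC.** A reader might infer that without a team term the pilot cannot inform the design of the larger trial. That does not follow. Team membership is known, so an ICC can be computed from the same data at any time. The Protocol also does not say that the full-scale trial will use teams, and ten teams estimate an ICC poorly.

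**The wording does not forbid other terms, and an SAP may add them.** This is partly fair. But the Protocol states which clustering the random effects address and mentions no other, although it describes the teams in detail. An SAP that followed that sentence would omit team. Covariate adjustment does not repair this, since no team variance component is named.

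**The cost is more than the square root of the design effect.** A reader might take the correct interval at ICC 0.05 to be 20% wider. With 9 df it is about 37% wider, and 14% wider even with no clustering. This stands and belongs in the cost.

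**With ten teams the variance will often be estimated as zero.** True, but the simulation above shows that the error rate still does not exceed 5%.

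**Conclusion.** The point holds in conditional form. The Protocol describes a team-delivered intervention and then specifies a model that recognises only within-person correlation. If changes are positively correlated within teams, the standard errors for the secondary-outcome changes are too small by a factor of √(1 + 9 × ICC): about 4%, 20% and 38% at assumed ICCs of 0.01, 0.05 and 0.10. The heterogeneity tests are affected as far as the factor clusters by team, with neighborhood SES the most exposed.

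The figures assume equal teams and a continuous change score analysed with a one-sample test. The planned three-time-point model was not simulated. The model should be changed because the remedy is cheap and uses data already held, but this does not undermine the pilot's primary purpose.

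**What to change.** In the secondary-outcomes paragraph of Analysis and Internal Validity, state that the model will include random effects for team and for team by time, in addition to the within-subject effects, with Kenward-Roger or Satterthwaite degrees of freedom. A team intercept alone is not enough, because it cancels out of the within-person change. Specify a t-test on the ten team-mean changes (9 df) as the confirmatory check, and say which result is reported if the team-by-time variance is estimated as zero. Apply the same structure to the heterogeneity models. State whether community health worker assignment coincides with team; if not, say how that second possible source of clustering will be handled.

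Optionally, report the team ICC of each change with its confidence interval, for use if the full-scale trial keeps team delivery. Note that ten teams estimate it imprecisely, so it should not be used as a point value.

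**Cost.** A short change to the text and no new data. Intervals widen by about 14% at ICC 0 and about 37% at ICC 0.05 on the 9-df analysis.

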## **Research Protocol:**

### **Creating Healthier Communities – AAMWI & OSU**

All statistical analyses will be performed using either SAS 9.4 or the most current version (SAS Institute, Inc., Cary, NC) or Stata 15 or the most current version (Stata Corporation, College Station, TX). Descriptive statistics (mean, median, standard deviation, proportions, etc.) of each of the collected variables will be estimated overall.

Sample Size and Power Analysis: This is a pilot study so sample size and power calculations were not performed. We will use data from this pilot study to solidify protocol parameters and estimate the degree of attrition that is considered in sample size and power calculation for a full-scale randomized controlled trial.

Missing Data: We expect missing data, for the post-intervention measures, where we expect a 10% attrition rate. We will carefully examine the pattern of the missing data and impute missing data via multiple imputation methods if missing completely at random (MCAR) mechanism is present. The mixed effects modeling approach described earlier allows for data missing at random (MAR). If the pattern of missing data indicates the potential missing not at random (MNAR), pattern-mixture modeling will be used. The robustness of findings under MCAR, MAR, and MNAR mechanisms will be evaluated.

Heterogeneity of Treatment Effect (HTE): To determine if there is HTE, we will extend our analysis models to include statistical interactions between participant factors and treatment and perform Wald tests of the interaction effect. Potential interaction factors include age, income, education level, neighborhood SES, and food insecurity. These analyses will be considered exploratory and thus no additional adjustment of p-values will be undertaken.

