## Research Protocol: Creating Healthier Communities – AAMWI & OSU

|    |                                                                                                                                                 |                                                    |                                                           |
|----|-------------------------------------------------------------------------------------------------------------------------------------------------|----------------------------------------------------|-----------------------------------------------------------|
| 21 | 
 
• Introduction to Global One Health Initiative (30 min)
 
• Physical Activity (45 min)
 
 | Global One Health Initiative                       | Weight, BP check                                          |
| 22 | 
 
• DPP Session 16: Ways to Stay Motivated (30 min)
 
• Physical Activity (45 min)
 
       |                                                    | Weight Check                                              |
| 23 | 
 
• The importance of 7-8 hours of sleep (30 min)
 
• Physical Activity (45 min)
 
         |                                                    | Weight Check                                              |
| 24 | 
 
• Introduction to ResearchMatch (30 minutes)
 
• Physical Activity 45 min
 
              | OSU Center for Clinical and Translational Sciences | Complete Surveys online via redcap Labs and Vitals |

| Table 2. Project Timeline and Outcomes |        |    |    |    |        |    |    |    |
|----------------------------------------|--------|----|----|----|--------|----|----|----|
|                                        | Year 1 |    |    |    | Year 2 |    |    |    |
| Milestone                              | Q1     | Q2 | Q3 | Q4 | Q1     | Q2 | Q3 | Q4 |
| IRB approval                           | •      |    |    |    |        |    |    |    |
| Recruitment/enrollment                 | •      | •  |    |    |        |    |    |    |
| CHW training                           | •      | •  |    |    |        |    |    |    |
| Intervention                           |        |    | •  | •  |        |    |    |    |
| Data analyses                          |        |    |    |    | •      | •  |    |    |

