### **Analysis and Internal Validity**

Analytic Methods: The analytic strategy will use intent-to-treat (ITT) analysis. Preliminary analyses include descriptive statistics to check the data quality, examine variable distribution, and summarize sample characteristics. All data anomalies identified will be fully investigated and remedial strategies will be considered as appropriate.

Non-research related data previously collected at prior African American Male Wellness Walks will be used as part of this research project. We will analyze the data to evaluate longitudinal trends in the ideal cardiovascular health metrics for African American males participating in the walks.

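### The default missing-at-random model for ResearchMatch participation is likely to report roughly the completers' rate, because men who leave early miss the only session named for it

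*Protocol*

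**What the plan says.** The study is single-arm: "we will enroll 100 AA male participants from the annual AAMWI walk/health fair" (Protocol, Research Structure). The prevalence of ResearchMatch participation is a secondary outcome, and more participation in clinical trials is one of the secondary objectives.

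Under Analysis and Internal Validity the protocol fixes three things that bear on this outcome:

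- The principle: "The analytic strategy will use intent-to-treat (ITT) analysis".
- The method, in the paragraph on secondary outcomes, where ResearchMatch prevalence is listed: "For each outcome, we will use mixed-effects linear modeling for repeated measures".
- The missing-data position, in the Missing Data paragraph: "We expect missing data, for the post-intervention measures, where we expect a 10% attrition rate", and then "The mixed effects modeling approach described earlier allows for data missing at random (MAR").

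The same paragraph goes on to provide a pattern-mixture model if the pattern of missingness points to data missing not at random (MNAR). It also promises, without condition, to check robustness under all three mechanisms.

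There are two routes to registration. In Table 1 the Week 24 row, the last of the curriculum, carries "Introduction to ResearchMatch (30 minutes"). Separately, under Research Structure, "The CHW will assist in activating individual participants to engage in primary care, social support services, and enrollment in ResearchMatch". That second route is not tied to any week. Week 15 covers clinical trials in general. The protocol does not say how registration status is established in men who leave.

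**The concern.** For an outcome such as weight or blood pressure, MAR is a workable default because a leaver's earlier values say something about his later ones. ResearchMatch registration is different. Part of the exposure meant to produce it comes in the last week, so leaving early removes that part. The model knows nothing of this. It fills a leaver's Week 24 value from men who stayed and could attend, adjusted only slightly for any earlier values.

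The main figure for this outcome would then carry an ITT label while sitting close to the rate among completers. It would tend to overstate what the programme achieved among the men it enrolled. The error grows with attrition and does not shrink with a larger sample. The modelling is also largely avoidable: registration is a yes/no act that can be counted over everyone enrolled.

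**Working it through.** The protocol states no ResearchMatch rate and no power calculation, so there is no figure of its own to reproduce.

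**Inputs**

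- Enrolled: 100 men (Research Structure).
- Attrition d = 10% ("where we expect a 10% attrition rate", Missing Data), so 100 × (1 − 0.10) = 90 completers.
- Completers' registration rate p and leavers' rate q: not in the protocol. Both are assumptions and are varied below.

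**Formula**

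True prevalence among enrolled men = (1 − d)p + dq. If the model assigns about p to leavers, it reports about p. The overstatement is p − [(1 − d)p + dq] = d(p − q).

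**Results at d = 10%**

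| p | True, q = 0 | Overstatement, q = 0 | Overstatement, q = p/2 | Overstatement, q = p |
|---|---|---|---|---|
| 20% | 18% | 2 points | 1 point | 0 |
| 40% | 36% | 4 points | 2 points | 0 |
| 60% | 54% | 6 points | 3 points | 0 |
| 80% | 72% | 8 points | 4 points | 0 |

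The ceiling is 10 points (p = 100%, q = 0). In relative terms the excess is 0.10/0.90 = 11.1% for q = 0 and 0.05/0.95 = 5.3% for q = p/2. If attrition exceeded the protocol's expectation, q = 0 would give 0.20/0.80 = 25% at d = 20% and 0.30/0.70 = 43% at d = 30%.

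**Does the mixed model really behave this way?**

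This was simulated with n = 100, 10% attrition, a random intercept, time as a category, 150 runs and a completers' target of 60% at Week 24.

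| Scenario | Model | True | Excess |
|---|---|---|---|
| No one registered before Week 24; leavers 0% | 60.1% | 54.1% | 6.0 |
| 30% of completers registered by Week 12; leavers 0% | 60.2% | 54.7% | 5.5 |
| 30% registered by Week 12 in both groups; leavers stay at 30% | 59.5% | 56.6% | 2.9 |
| 30% of completers by Week 12; leavers stay at 15% | 59.6% | 55.4% | 4.2 |

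The model stays near the completers' rate in all four, including those with substantial registration by mid-programme. The result therefore does not depend on assuming that almost nobody registers before Week 24. The excess is about 3 to 6 points, in line with the formula.

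**Scale against sampling error**

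The 95% half-width with 90 completers is 1.96 × √(p(1 − p)/90): 8.3 points at p = 20% or 80%, and 10.1 points at 40% or 60%. At the protocol's attrition the overstatement in the table above is no larger than this.

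**The case against.** The strongest reply has four parts.

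- **The plan does not stop at MAR.** A reader who takes the MAR sentence alone might infer that leavers are handled only that way. The documents do not support that: the pattern-mixture provision and the unconditional robustness check follow directly. This stands. But the pattern-mixture model depends on what the observed pattern suggests, and observed data cannot separate MAR from MNAR. The robustness check is a sensitivity analysis. Neither changes the main estimate or its denominator.
- **Missing the session is not the same as not registering.** A reader might infer that MAR fails by design, or that leavers cannot have registered. The protocol does not say so: community health workers assist enrolment at no fixed time, and Week 15 already introduces clinical trials. This also stands. Lower uptake among leavers is likely, not established.
- **The data may not be missing at all.** If status can be established for every enrolled man from study records, nothing needs filling in, and an ITT reading already gives the right denominator. That is possible, and it is what the fix makes explicit. As written, the stated method for this outcome is the mixed model, and the protocol does not say that leavers' status will be sought.
- **Counting unknown as not registered is itself an untestable assumption, and it errs downward.** True. The error is confined to men who left and registered without the study's knowledge, and the model-based rate can be shown beside it.

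The point also concerns one secondary outcome in an unpowered pilot, with no decision threshold attached. That limits its weight.

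**Conclusion.** The concern holds in a limited form. The stated default analysis gives leavers roughly the completers' registration rate, although the schedule already gives a reason to expect a lower one. If leavers do register less often, the main ResearchMatch estimate overstates prevalence among enrolled men by d(p − q). At 10% attrition that is 2 to 8 points across completers' rates of 20% to 80% with no leaver registering, half that if leavers register at half the rate, and nothing if they register equally. Only the 10% comes from the protocol; p and q are assumed.

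It would go too far to say that the reported figure will certainly be inflated, or that the plan has no answer to MNAR data. The bias is modest and at or within the sampling error at the expected attrition. It is worth correcting because a direct count is simpler than the model and its denominator is unambiguous.

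**What to change.** In the secondary-outcomes and Missing Data paragraphs of Analysis and Internal Validity, define the main ResearchMatch estimate separately from the mixed model:

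- **Numerator:** men with evidence of registration by Week 24 from any of survey, community health worker records or study records.
- **Denominator:** all men enrolled.
- **Interval:** exact binomial.
- **No evidence:** counted as not registered, whether or not the man completed the programme.
- **Sensitivity analysis:** the completers' rate or the MAR model rate, shown alongside.

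Under this rule, registration through a community health worker before leaving is credited wherever a record exists.

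The cost is about a sentence of analysis wording and a status check for each enrolled man, including those who left. The downside is slight undercounting if a man who left registered without the study knowing.
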